### Sample size calculation

Literature indicates various effect sizes of feedback from ROM
[17,21,27,62]. The present study was powered to detect the upper limit of a small effect size (f = 0.15; ANCOVA). A power analysis using G*Power
[63] indicated that a total sample size of 432 (n = 144 per condition) would be sufficient to detect significant (α = .05, power = .80) condition effects on symptom severity (3 conditions, including testing for 3 covariates and possible interaction effects).

However, our previous experiences have shown that approximately 50% of the participants stop filling out questionnaires after one measurement (baseline assessment). Hence, the clinicians of these children, adolescents and parents do not receive feedback during treatment. It would not be desirable to impute 50% of the data as this would make the imputation highly unreliable. Therefore, we will invite twice as many children, adolescents and parents (n = 288 per condition and 864 in total) to include the required number of 144 participants per condition of whom clinicians have received feedback during treatment (i.e. at least 50% of the measurements).

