### Randomization

Randomization of each participant to one of the three feedback conditions will be carried out using a computer-generated random number list with a blocked randomization scheme (block size 6, randomization ratio [1:1:1]). An independent researcher will allocate the participants to the feedback conditions after the baseline assessment. To ensure that the distribution of parents and children and adolescents is similar across the three feedback conditions, randomization will be stratified by age of the child or adolescent (4 to 11 years old and 12 to 17 years old). To exclude confounding due to differences among departments, randomization will also be stratified by department (Arnhem, Ede, Nijmegen and Tiel).

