### Statistical analyses

All analyses will be conducted using Mplus
[64], because this program allows analyses of complex data while taking into account the longitudinal character of the data. Intervention effects will be analyzed according to the intention-to-treat principle and the completers-only framework. For the intention-to-treat analysis, missing data will be handled using multiple imputations (MI). Descriptive statistics will be calculated for all variables of interest (e.g. symptoms, quality of life, satisfaction with treatment, number of sessions, length of treatment, dropout rate). In order to assess whether randomization resulted in equal groups, we will examine whether there are differences among the three feedback groups on relevant covariates (e.g. sex, age, educational level, ethnicity, socioeconomic status, marital status, household composition and diagnosis) using ANOVA for the continuous variables and Chi-Square tests for the categorical variables. Variables that are distributed differently among the three groups will be entered as control variables in all models testing the effects of the feedback conditions. The hypotheses will be tested using multivariate linear regression analyses. In addition, we will examine whether being NOT moderates the association between the feedback intervention and symptom severity. Therefore, interaction terms will be calculated as the product of the feedback condition and whether or not the client is NOT. These terms will be added as a second step in the multivariate analyses. Reporting of the results of the study will be in accordance with the CONSORT statement
[65,66].

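### Doubling recruitment leaves about half the SDQ outcomes missing after randomisation, so the intention-to-treat analysis relies on imputation the plan rejects, and the 80% power belongs to a subset formed after allocation

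*Protocol article*

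**What the plan says.** Four parts of the protocol article bear on this.

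- **Power (Sample size calculation).** The calculation gives "a total sample size of 432 (n = 144 per condition" and claims that this "would be sufficient to detect significant (α = .05, power = .80) condition effects on symptom severity", with f = 0.15.
- **Expected loss (same section).** From earlier experience, about half the participants are expected to complete only the baseline questionnaires. The authors decline to fill that gap statistically: "It would not be desirable to impute 50% of the data as this would make the imputation highly unreliable". They will instead invite 288 per condition (864 in all), to end with "144 participants per condition of whom clinicians have received feedback during treatment (i.e. at least 50% of the measurements".
- **Timing (Randomization; also Participants).** "An independent researcher will allocate the participants to the feedback conditions after the baseline assessment".
- **Analysis (Statistical analyses).** Effects will be analysed by intention to treat and also in completers only. Neither is named as primary. "For the intention-to-treat analysis, missing data will be handled using multiple imputations (MI").

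The Abstract, Trial design and Participants sections give 144 per condition as the number allocated, not 288.

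**The concern.** Because allocation follows baseline, clients who stop after baseline have already been randomised. Inviting more people raises the number observed but cannot change the proportion lost. An intention-to-treat analysis of all randomised clients must then impute roughly half of the primary outcome, which the sample size section says should not be done. If the analysis is confined to those who stayed, it is no longer intention-to-treat.

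The stated power is tied to clients whose clinicians received feedback during treatment. That cannot be known at allocation, so the powered set is not a randomised comparison. Comparing such clients, or completers, is open to selection bias if staying relates to outcome and the relation or the retention rate differs by arm.

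The article gives reasons to take this seriously. Background attributes many treatment dropouts to a perceived lack of benefit. Aims and hypotheses predicts less treatment dropout in conditions 2 and 3. Strengths and limitations concedes that clinicians are not blinded. Treatment dropout is not the same as stopping questionnaires, but it is a plausible route to it.

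At stake are the validity of the primary result and which population the 80% power describes.

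**Working it through.** **1. Reproduce the plan's figures.** Inputs from Sample size calculation: f = 0.15, α = 0.05, power 0.80, 3 conditions, 3 covariates. Use the noncentral F with df1 = 2, df2 = N − 3 − 3 and noncentrality N·f². At N = 432 the noncentrality is 432 × 0.0225 = 9.72 and power is 0.8007. The smallest N reaching 0.80 is 432, as stated. Inflation for 50% loss: 144/(1 − 0.5) = 288 per condition and 432/(1 − 0.5) = 864. The arithmetic is right.

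**2. Missing share before and after doubling.**

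| Randomised | Observed after 50% loss | Missing | Share missing |
|---|---|---|---|
| 432 | 216 | 216 | 50% |
| 864 | 432 | 432 | 50% |

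Doubling changes the second column and leaves the last one alone.

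**3. Power for all randomised clients.** The documents do not give the effect in clients who stop after baseline, so two cases are shown.

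- *f = 0.15 in everyone randomised; half the information lost, so effective N = 432:* power 80.1%.
- *No effect in the half without feedback during treatment (assumption):* the mean differences halve, so f ≈ 0.075. With all 864 outcomes observed, noncentrality is 864 × 0.005625 = 4.86 and power is 49.0%; 80% would need 1,716. With an effective N of 432, power is 26.5%.

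If instead only 432 are randomised, as the Abstract, Trial design and Participants sections read, 216 are observed and power at f = 0.15 is 48.6%.

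**4. Possible bias in a comparison of those who stay.** The article has no data on retention by arm, so these are assumed examples. Let retention be r, c the standard normal cut-off exceeded with probability r, φ the standard normal density, and ρ the correlation between staying and outcome. The mean outcome among stayers then shifts by ρ·φ(c)/r SD.

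- *Same ρ = 0.3, retention 50% versus 40%:* 0.3 × 0.399/0.5 = 0.239; 0.3 × 0.386/0.4 = 0.290; difference 0.05 SD.
- *Retention 50% in both arms, ρ = 0.3 in one and 0 in the other:* 0.239 − 0 = 0.24 SD.

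For scale, if the three means are equally spaced (also an assumption), f = 0.15 implies an adjacent-arm difference of 0.15/√(2/3) = 0.18 SD.

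**The case against.** Several objections have force.

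- **Inflating for loss is ordinary practice, and doubling does help.** It gives an imputation model 432 observed cases instead of 216, and power is about 80% if f = 0.15 holds throughout. This stands as to precision. It does not answer the missing share, which is what the plan itself objects to.
- **Inviting may come before randomisation.** The number randomised is indeed unsettled. That does not rescue the plan, because receipt of feedback during treatment cannot be known at allocation.
- **A SAP may rank the analyses and specify the imputation model.** That is fair, and the lack of a ranking alone would be minor. No SAP can make both sections of this article true as written.

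A reader might also infer more than the documents support:

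- *That the extra form is shown to drive clients out of conditions 2 and 3, at 45 against 30 minutes.* Procedure's 45 minutes includes the satisfaction questionnaire, which every arm completes at the end of treatment. Clients who stop after baseline, before allocation has taken effect, have probably not met the extra form.
- *That half of all outcomes are missing.* Sessions, treatment length and dropout are registered, not self-reported (Secondary outcome measures). The problem concerns the questionnaire outcomes.
- *That the analysis is formally restricted to clients with half or more of their measurements.* That phrase defines the recruitment target. Statistical analyses neither limits the intention-to-treat set to it nor defines completers by it.
- *That the bias is known to be large.* The 0.24 SD case needs a correlation in one arm and none in another, and neither example allows for covariate adjustment.

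**Conclusion.** The point holds for the primary outcome and the other questionnaire outcomes. The article rejects imputing half the data, adopts a remedy that leaves about half missing, and then plans an intention-to-treat analysis that imputes it. This rests on the article's own approximate 50% and on intention-to-treat meaning all randomised clients. If it means only those retained, less is imputed, but the analysis is not intention-to-treat and the selection problem remains.

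The 80% power attaches to a subset defined after randomisation. For all randomised clients it ranges from about 80% (f = 0.15 throughout, effective N 432) to about 49% with complete outcomes on 864 if those without feedback during treatment gain nothing, and lower still with half the outcomes missing.

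Selection bias is a risk of unknown size. The assumed examples, 0.05 to 0.24 SD, run from about a quarter of the 0.18 SD benchmark to more than all of it. The documents do not show that retention differs by arm.

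**What to change.** - Name the comparison of all randomised clients, in their allocated arm, as the primary analysis. Use every available SDQ score, by likelihood estimation or by multiple imputation with auxiliary variables from the patient file: sessions, treatment length, unilateral ending and diagnosis.
- Add a delta-adjusted sensitivity analysis. Likelihood and multiple imputation both assume data missing at random, so changing from one to the other does not remove the difficulty. Under that assumption, clients who stop are modelled on those who stay, although the article says their clinicians get no feedback during treatment.
- Make completers-only a sensitivity analysis, and drop receipt of feedback on half or more of the measurements as the rule for counting toward the sample size.
- State whether 432 or 864 are randomised, and align the Abstract, Trial design, Participants and Sample size calculation sections.
- Restate power for the intention-to-treat set, with the assumed effect in clients who stop after baseline. Report retention by arm.

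The cost is protocol and SAP wording and some analysis time. The drawback is a stated power that may fall below 80%. These changes make that visible but do not restore it; if the diluted effect is judged realistic, 864 would not be enough.

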**Methods/Design:**

We will examine three different forms of feedback through a three-arm parallel-group randomized controlled trial. 432 children and adolescents (aged 4 to 17 years) and their parents, who have been referred to mental health care institution Pro Persona, will be randomly assigned to one of three feedback conditions (144 participants per condition). Randomization will be stratified by age of the child or adolescent and by department. All participants fill out questionnaires at the start of treatment, one and a half months after the start of treatment, every three months during treatment, and at the end of treatment. Participants in the second and third feedback conditions fill out an additional questionnaire. In condition 1, clinicians receive basic feedback regarding clients’ symptoms and quality of life. In condition 2, the feedback of condition 1 is extended with feedback regarding possible obstacles to a good outcome and with practical suggestions. In condition 3, the feedback of condition 2 is discussed with a colleague while following a standardized format for case consultation. The primary outcome measure is symptom severity and secondary outcome measures are quality of life, satisfaction with treatment, number of sessions, length of treatment, and rates of dropout. We will also examine the role of being not on track (not responding to treatment).

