**Figure 1 F1:**
[figure not shown]
Study design.

The trial will be conducted at mental health care institution Pro Persona. All outpatient youth departments (in Arnhem, Ede, Nijmegen and Tiel) will participate and all families with children and adolescents between the ages of 4 and 17 years will be approached to participate. If the child is between 4 and 11 years old, the parents will be approached to participate in the study. If the child or adolescent is between 12 and 17 years old, the child or adolescent will be approached to participate in the study. Children under 16 years of age will only be approached to participate after parental consent for participation in the study is obtained. Children, adolescents and parents who agree to participate will sign an informed consent form. The participants will be randomly allocated to one of the three feedback conditions (144 participants per condition; randomization ratio [1:1:1]). All participants will fill out web-based questionnaires and their clinicians will receive feedback about the results. Clinicians will have to discuss the feedback with the participants during treatment. Participants will not receive incentives for completing the questionnaires, as this trial is part of the regular ROM within the institution. Ethical approval has been granted by the ethical committee of the Faculty of Social Sciences at the Radboud University Nijmegen (ECG 2012-1304-031).

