### Participants

The study will take place in all of Pro Persona’s outpatient youth departments (in Arnhem, Ede, Nijmegen and Tiel). Pro Persona is a specialised mental health care institution in the Netherlands that offers outpatient and inpatient treatment for children, adolescents, adults and the elderly. Approximately 110 clinicians work in the outpatient youth departments. These clinicians are social workers, social psychiatric nurses, nurse practitioners, educationists, psychologists, health care psychologists (GZ-psychologen), clinical psychologists, psychiatrists and physicians.

All families with children and adolescents between the ages of 4 and 17 years who are referred to Pro Persona’s outpatient youth departments receive information about the study. We will include children and adolescents with any kind of mental health problems (e.g. developmental, anxiety or mood disorders) and any kind of treatment (e.g. individual or group treatment, cognitive-behavioural or solution-focused treatment, frequent or irregular treatment). On average, 33% of the treatments in youth mental health care last less than 3 months, 35% last from 3 to 12 months and 31% last more than a year
[47]. The only exclusion criterion will be child’s, adolescent’s or parent’s insufficient understanding of the Dutch language. If the child is between 4 and 11 years old, the parents will be approached to participate in the study, because younger children are less able to fill out questionnaires and parents are legally responsible for the children. If the child or adolescent is between 12 and 17 years old, the child or adolescent will be approached to participate in the study. Children and adolescents under 16 years of age will only be approached to participate after parental consent for participation in the study is obtained. Children, adolescents and parents who agree to participate will sign an informed consent form. Participants will be randomly allocated to one of the three feedback conditions (144 participants per condition), using a block randomization scheme. Randomization will be carried out by an independent researcher after the baseline assessment.

We are aware that prior research has shown systematic discrepancies between multiple informants with regard to the nature and severity of children’s and adolescents’ symptoms

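### Three places give the number needed after attrition (144 per condition, 432 in all) as the number randomised, but the protocol's own 50% loss requires 864 randomised

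*Protocol article*

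**What the plan says.** Three places describe the number randomised. The abstract gives a total of 432 who "will be randomly assigned to one of three feedback conditions (144 participants per condition"). The Trial design section, after Figure 1, allocates "144 participants per condition; randomization ratio [1:1:1"]. The Participants section says: "Participants will be randomly allocated to one of the three feedback conditions (144 participants per condition"). The total of 432 is printed as a number randomised only in the abstract; the other two places give it per condition.

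The Sample size calculation section uses the same 432 differently. It finds that "a total sample size of 432 (n = 144 per condition) would be sufficient to detect significant" condition effects, and then reports from experience that "approximately 50% of the participants stop filling out questionnaires after one measurement (baseline assessment"). It rejects imputing half of the data. It concludes: "Therefore, we will invite twice as many children, adolescents and parents (n = 288 per condition and 864 in total"). The stated purpose is to end with 144 per condition whose clinicians received feedback during treatment, defined as half or more of the measurements.

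The Participants and Randomization sections both place randomisation after the baseline assessment.

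**The concern.** The same 144 per condition is the number entering the randomised comparison in three sections and the number left after a 50% loss in a fourth. Because allocation follows baseline and the loss follows allocation, it cannot be both.

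A team that closes randomisation at the figure in the abstract would end with about half the information that the power calculation assumes. The denominator for the promised CONSORT reporting is also unclear: a reader cannot tell whether 432 is the randomised cohort or a subset formed after randomisation.

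The choice of verb adds a smaller problem. In the Procedure section, invitations go to people who have signed consent, and the first one is to the baseline assessment itself. An invited person is therefore not yet a randomised one.

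**Working it through.** **Inputs, all from the Sample size calculation section unless noted**
- Effect size: "The present study was powered to detect the upper limit of a small effect size (f = 0.15; ANCOVA").
- Test settings: "α = .05, power = .80) condition effects on symptom severity (3 conditions, including testing for 3 covariates and possible interaction effects").
- Required number with data: 432 (144 per condition).
- Expected loss after baseline: about 50%.
- Inflated number: 864 (288 per condition).
- Randomisation after baseline: Participants and Randomization sections.

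**Step 1: reproduce the 432.** For a fixed-effects ANCOVA, power = P(F′ > F_crit), where F′ is noncentral F with df1 = 3 − 1 = 2, df2 = N − 3 groups − 3 covariates, and noncentrality λ = f² × N.
- N = 432: λ = 0.0225 × 432 = 9.72, df2 = 426, power = 0.8007.
- N = 431: power = 0.7998.

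So 432 is the smallest N that reaches 80%. The stated figure reproduces.

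**Step 2: reproduce the inflation.** 432/(1 − 0.5) = 864, and 144/(1 − 0.5) = 288 per condition. This also reproduces.

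**Step 3: locate the loss.** The order is baseline, then randomisation, then about 50% stopping. Those who stop are randomised participants, so the 864 in step 2 has to be the number randomised.

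**Step 4: follow the three other sections literally.** 432 randomised × 0.5 = 216 with in-treatment data. Then λ = 0.0225 × 216 = 4.86, df2 = 210, and power = 0.486.

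**Step 5: how much reserve does 864 leave?** If all 864 complete baseline and are randomised, expected retention is 864 × 0.5 = 432 and power is 0.80. With retention of exactly 50%, the binomial probability of keeping at least 432 is 0.51, and of keeping at least 144 in every condition 0.14. The plan meets its target on average and has nothing in hand.

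**Step 6: the retention rule is stricter than the loss allowed for.** The Procedure section expects one-third of clients to have one measurement during treatment, one-third four, and one-third at least five.
- One in-treatment measurement: a client who answers baseline and that one has 2 of 3, counting the end-of-treatment measurement, and meets the rule.
- Four in-treatment measurements: a client who answers baseline and one more, then stops, has 2 of 6 (or 1 of 4 if only in-treatment measurements count). This client is outside the baseline-only half yet fails the rule.

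Later loss can therefore matter for about two-thirds of clients, and the factor of two does not cover it. The protocol gives no rate for it.

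**The case against.** The strongest reply is that the intention can be recovered. The sample size section is the operative one, it plans for 864, and it says what the 144 per condition is meant to be. A team would have to overlook that section to stop at 432. This stands as a reason to call the problem a labelling inconsistency rather than a calculation error. It does not remove the contradiction, because three sections attach the number to the act of allocation and none qualifies it.

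A second reply is that the 0.49 describes clients with in-treatment data, whereas the Statistical analyses section also plans an intention-to-treat analysis with multiple imputation. That is so. But clients with only a baseline contribute little outcome information to any imputation, and the sample size section itself regards imputing half of the data as unreliable.

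A reader might go further and infer that 864 invitations cannot yield 432 or 80% power, since some families will decline or fail the language criterion. The document does not support this. The 864 is broken down as 288 per condition, and families have no condition until they are allocated. The Procedure section also uses the verb for people who have already consented. Both favour reading 864 as enrolled or allocated, and on that reading 432 and 80% power follow. A shortfall would need a baseline-completion rate that is not given. As pure assumptions, 90%, 70% and 50% completion among 864 would leave 388, 302 and 216 with data, and power of 0.75, 0.64 and 0.49. These show why the word needs settling; they are not evidence of a shortfall. Likewise, the rule on half of the measurements supports saying that there is no margin, not that power is lost by a stated amount.

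**Conclusion.** The stated number randomised is wrong as written in the abstract, Trial design and Participants sections. By the protocol's own attrition figure and its own timing of randomisation, 864 must be randomised (288 per condition) for about 432 to have in-treatment data. Randomising 432 would leave about 216 and give power of about 0.49 instead of 0.80.

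This rests only on figures in the document: f = 0.15, α = 0.05, three conditions, three covariates, and 50% stopping after baseline. The power calculation and the doubling are both correct.

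The wording used for the 864 is ambiguous rather than wrong. The number suffices in expectation only if all 864 complete baseline and are randomised, and it leaves nothing for later loss under the retention rule.

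**What to change.** - State one target throughout: 864 randomised after a completed baseline assessment, 288 per condition.
- In the abstract, Trial design and Participants sections, label 432 (144 per condition) as the number expected to have in-treatment data.
- In the Sample size calculation section, replace *invite* by *randomise*.
- If 864 cannot be randomised, restate the power for the number expected to have data.

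The cost is wording, since the protocol already plans for 864. The only substantive cost arises if 864 is out of reach, because a power below 0.80 must then be reported.
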